**Study Population**

We will identify all male patients over the age of 18 with an incident exposure to a PDE5 inhibitor from 1^st^ July 1999 to 1^st^ August 2014 inclusive. The reasoning behind the proposed study period is that the restrictions regarding the prior diagnoses required to receive a PDE5 inhibitor prescription were imposed on 1^st^ July 1999, and restrictions for generic sildenafil were lifted on 1^st^ August 2014, after Pfizer’s sildenafil patent expired on 21^st^ June 2013. Follow up will begin at the date of first PDE5 inhibitor prescription (hereafter the “index date”). Exposed patients will matched to up to four controls on age at first prescription (within 3 years in either direction), GP practice, diabetes status, and their index date will be the same as their matched case’s. All matching variables will be measured at the index date. Patients with any cancer diagnoses prior to the index date will be excluded. Individuals selected as controls may later go on to start a PDE5 inhibitor; in this situation they will be censored as a control at the time of starting a PDE5 inhibitor, and they will contribute separately as an exposed patient from that time point (with their own matched controls).

**Sample size/power calculation**

Preliminary feasibility analyses suggest that there will be approximately 179,298 men with incident sildenafil prescriptions in the study population. The prevalence of malignant melanoma among these patients is ~0.27%. With each exposed patient matched to one control, the study would have 80% power to detect an effect size of approximately 1.18, at a significance level of 5%; our higher intended matching ratio will increase the power further. This shows that our study will be highly powered to detect an effect size similar to that observed by Li et al.

**Exposures and outcome**

*Exposure*

- Primary exposure – Ever received a PDE5 inhibitor prescription (time-updated)

An incident PDE5 inhibitor prescription will be identified by an appropriate therapy code in the patient’s therapy records (relevant code list in appendix 1). To be considered incident, the first prescription must be at least 12 months after initial registration into CPRD as prescriptions within this period could be continuation of a prescriptions from a prior GP, of unknown duration. All matched controls must also have one year of post registration follow up prior to index date.

- Secondary exposure – Cumulative number of PDE5 inhibitor prescriptions (time-updated)

All subsequent prescriptions will be identified and the cumulative number of prescriptions will be categorised into the following groups: 1, 2-4, 5-10, 10-20 and 20+.

Number of prescriptions prescribed to patients will be used as a secondary exposure instead of cumulative duration of prescription because PDE5 inhibitors are prescribed for a patients to take as required. We are unable to judge the sexual activity of patients, hence any estimations made in an attempt to identify the length of time until a patient runs out of tablets will be unreliable. As a further analysis we will use the cumulative number of tablets prescribed to a patient as an exposure.

*Outcome*

The primary outcome is incident malignant melanoma, identified by an appropriate Read code in the patients’ medical record (relevant code list in appendix 2).

**Statistical/analysis plan**

Within the cohort, a patient’s observation time will begin at the index date and will end when one of the following occur: incident malignant melanoma, at diagnosis of a cancer other than malignant melanoma, death, transfer out of CPRD network, prescription of a PDE5 inhibitor (for unexposed controls), or end of follow up. The following analyses will be carried out using incident malignant melanoma as the primary outcome.

*Descriptive analyses*

Prior to exploring the relationship between PDE5 inhibitors and malignant melanoma, we will firstly describe the distribution of exposed and unexposed within the following variables: age, ever prescribed a PDE5 inhibitor, GP practice region (North East, North West, Yorkshire & the Humber, East Midlands, West Midlands, East of England, South West, South Central, London, South East Coast, Northern Ireland, Scotland, Wales), diabetes status, smoking status (non-smoker, current smoker, ex-smoker), BMI (underweight, normal, overweight/obese), alcohol status (non-drinker, current drinker, ex-drinker), index of multiple deprivation score.

*Ever exposed vs. never exposed to a PDE5 inhibitor*

Crude incidence ratios will firstly be calculated. The main exposure variable will then be included in an unadjusted and adjusted Cox regression model (see “Confounding” below), stratified by matched set to account for the matching. The primary outcome will be a diagnosis of incident melanoma and patients will be censored at diagnosis of any other cancer, death, transfer out of the CPRD network, or on 21^st^ June 2013 (end of follow up). Hazard ratios and 95% confidence intervals will be estimated, comparing the rate of incident melanoma between patients who have ever been prescribed a PDE5 inhibitor and patients that have never been prescribed a PDE5 inhibitor. We will also calculate changes in absolute risk of melanoma by obtaining predictions from a Poisson model with the same covariates as our main Cox model, plus time since index date (time-updated).

*Cumulative duration of exposure*

Unadjusted and adjusted Cox regression models will then be re-run using a time updated variable capturing the cumulative number of PDE5 inhibitor prescriptions in place of the ever exposed variable. Hazard ratios and 95% confidence intervals will again be estimated.

*Confounding*

Age, GP practice, diabetes status and calendar time are matching variables. Our models will also be adjusted for the following potential confounders evaluated at beginning of follow up:

- Smoking status (never-smoker, current smoker, ex-smoker)
- BMI (underweight, normal, overweight, obese)
- Alcohol status (never-drinker, current drinker, ex-drinker)
- Index of multiple deprivation score

*Interaction*

We will fit interaction terms to explore possible effect modification between exposure to a PDE5 inhibitor and age, smoking status and index of multiple deprivation score.

*Sensitivity analysis*

As a sensitivity analysis we will exclude the first 12 months of follow up after index date in both exposed and unexposed patients. This is to decrease the chance of reverse causality, whereby undiagnosed melanoma cancers cause ED and hence the need for a PDE5 inhibitor prescription.

We will also conduct an analysis restricted to patients diagnosed with diabetes as previous restrictions mean all patients diagnosed with diabetes were definitely eligible for a PDE5 prescription.

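### Initiators are accepted to 1 August 2014 but all follow-up is censored on 21 June 2013, so 13 months of initiators would enter after their own end of follow-up and all later events would be lost

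*Combined protocol and SAP*

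**What the plan says.** Study Population admits men with "incident exposure to a PDE5 inhibitor from 1^st^ July 1999 to 1^st^ August 2014 inclusive". It presents this interval as the study period and justifies its end: "restrictions for generic sildenafil were lifted on 1^st^ August 2014". The same sentence mentions the other date only as background, "after Pfizer’s sildenafil patent expired on 21^st^ June 2013".

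Entry is defined there too. "Follow up will begin at the date of first PDE5 inhibitor prescription", and for controls "their index date will be the same as their matched case’s".

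Statistical/analysis plan gives the end of observation twice. Its opening sentence closes the list of stopping events with "prescription of a PDE5 inhibitor (for unexposed controls), or end of follow up", without a date. The subsection on ever versus never exposure then dates it: patients are censored at an event "or on 21^st^ June 2013 (end of follow up"). No reason is given for choosing the patent-expiry date. The cumulative-prescription models re-run the same Cox models with a different exposure variable, so they inherit that date.

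The closing section on changes from the protocol alters neither date and reports that, apart from the listed changes, the analyses followed the plan.

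**The concern.** Entry is allowed for 13 months after exit has been imposed. Applied as written, anyone starting a PDE5 inhibitor after 21 June 2013 contributes zero or negative time. His controls share his index date, so the whole matched set drops out. Every other man still under observation on that date loses up to 13 months of person-time and any melanoma diagnosed in it.

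Three things are at stake.

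- **Reproducibility.** Two analysts following this text could build different cohorts, with different exposed numbers, person-time and melanoma counts, for the primary hazard ratio. The study describes itself as hypothesis testing, so the cohort should not depend on a choice made during analysis.
- **The power statement.** It rests on "approximately 179,298 men with incident sildenafil prescriptions in the study population", but the number that could be analysed depends on which date governs.
- **The secondary analyses.** The lost time is each man's latest follow-up, when his cumulative prescription count is highest. In the sensitivity analysis that drops the first 12 months, men starting after about 21 June 2012 would also contribute nothing.

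**Working it through.** **Inputs.** Accrual from 1 July 1999 to 1 August 2014 (Study Population); end of follow-up 21 June 2013 (Statistical/analysis plan); 179,298 exposed, melanoma about 0.27%, 1:1 matching, 80% power, 5% significance, detectable effect about 1.18 (Sample size/power calculation).

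**1. The plan's power figure.** Two proportions, two-sided 5%, n = 179,298 per group, taking 0.27% as the control proportion: p1 = 0.0027, p2 = 1.18 × 0.0027 = 0.003186, mean p̄ = 0.002943.

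Power = Φ{[√n·(p2 − p1) − 1.96·√(2p̄(1 − p̄))] / √(p1(1 − p1) + p2(1 − p2))} = Φ{[423.4 × 0.000486 − 1.96 × 0.0766] / 0.0766} = Φ(0.726) = 76.6%.

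Power reaches 80% at a ratio of 1.188. If 0.27% is instead the exposed proportion, power at 1.18 is 69.6% two-sided or 79.6% one-sided, and the two-sided detectable ratio is 1.208. The plan does not state sidedness. Its approximate 1.18 is close enough to serve as a baseline.

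**2. The gap.** 1 July 1999 to 21 June 2013 is 5,104 days (13.97 years); to 1 August 2014 it is 5,510 days (15.09 years). Difference: 406 days, or 13.3 months. 406 / 5,510 = 7.37%.

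**3. Initiators with no follow-up.** The documents give no initiation counts by calendar time, so these rest on assumptions. Let r = 5,104 / 5,510 = 0.9263.

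- Uniform initiation: (1 − r) × 179,298 = 0.0737 × 179,298 ≈ 13,211.
- Linearly rising from zero: (1 − r²) × 179,298 = 0.1419 × 179,298 ≈ 25,449.
- If 5% to 15% of initiators start in the gap: about 9,000 to 26,900.

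**4. Person-time lost, ignoring death and transfer.**

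- Uniform: mean administrative follow-up per initiator falls from 15.09/2 = 7.54 years to 13.97²/(2 × 15.09) = 6.47 years. Loss = 1 − r² = 14.2%.
- Linearly rising: loss = 1 − r³ = 20.5%.

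With uniform initiation and constant attrition at rate λ per year, person-time to horizon x is proportional to [x − (1 − e^(−λx))/λ]/λ. The loss is 13.3%, 12.8%, 12.1% and 11.3% for λ = 3%, 5%, 8% and 12%. The range under uniform initiation is therefore about 11% to 14%.

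**5. Events lost.** If the 0.27% is read as cases arising during follow-up to 1 August 2014, the exposed group has 179,298 × 0.0027 ≈ 484. With a constant hazard, 11.3% to 14.2% of these is about 55 to 69.

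**6. Detectable ratio at 1:1.** The log ratio scales with 1/√(fraction of events kept); ln 1.18 = 0.1655.

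- Uniform: exp(0.1655/√0.858) = 1.196.
- Linearly rising: exp(0.1655/√0.795) = 1.204.

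Starting from the recomputed 1.188, an 11% to 14% loss also gives about 1.20; from 1.208 it gives 1.22 to 1.23.

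**7. At the planned maximum of four controls.** The variance of the log ratio scales by 1.25/2 relative to 1:1. From 1.18, the detectable ratio is exp(0.1655 × √0.625) = 1.14 before the loss, 1.15 after a 14.2% loss and 1.16 after a 20.5% loss. By the two-proportion method, with an 11% to 14% loss, power for 1.18 falls from 88% to 83–84% (0.27% in the exposed) or from 93% to 89–90% (0.27% in controls).

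**The case against.** The best defence is that 21 June 2013 is a drafting slip. Study Population presents the interval ending on 1 August 2014 as the study period and gives a reason for its end; the other date appears there only as the patent expiry; and the first mention of end of follow-up in the analysis section is undated. On that reading the analysts followed patients to 1 August 2014 or later and nothing was lost. This is plausible, but nothing in the documents confirms it, and the changes section, which was the place to correct it, is silent. The losses computed here follow only if the stated date was applied. The contradiction stands either way.

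Second, no bias is shown. The cut-off is the same calendar date for exposed men and controls, and a matched set shares one index date, so sets in the gap drop out whole and the others are cut at the same point. That is right: the demonstrated harm is to precision and executability.

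Third, the move from 1.18 to 1.20 is for 1:1 matching, whereas up to four controls are planned. At full 1:4 the detectable ratio stays below 1.18 even after the loss. That also stands, subject to the matching ratio actually achieved.

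Fourth, the counts rest on assumed initiation patterns, and the 179,298 is an approximate feasibility count of sildenafil initiators, whereas the exposure is any PDE5 inhibitor. Both points limit how exactly the loss can be stated. Neither removes it.

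**Conclusion.** The concern holds. The accrual window and the censoring date contradict each other in the primary analysis, and no section reconciles them. Applied literally, the plan excludes everyone starting in the last 406 days of accrual together with their controls, and discards all later melanomas.

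Under the labelled assumptions this removes about 13,200 initiators and 11% to 14% of person-time (uniform initiation, with or without attrition), or about 25,400 initiators and 21% (linear rise, no attrition). The effect on power is modest, and planned matching at up to 1:4 would offset it. The point must still be fixed because the primary analysis cannot be carried out as written, and because a reader cannot tell which cohort produced the reported hazard ratio.

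**What to change.** Use one date throughout. The simplest change is to keep accrual to 1 August 2014 and amend the censoring rule in the ever-versus-never subsection so that follow-up ends no earlier than 1 August 2014. Follow-up to the last data collection date of the extract, if later, is a separate design choice and should be stated explicitly. If 21 June 2013 was truly intended, close accrual on that date as well, give the reason, recount the 179,298 and restate the detectable effect.

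In either case, put the same date in the opening sentence of Statistical/analysis plan, and record in the changes section which date the completed analysis used.

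The cost is one line of plan text and, if the 2013 date was applied while accrual ran to 2014, a rerun of the censoring step and the models that depend on it. No new data are needed.

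### As written, the Poisson model for absolute risk has no term for age, calendar period, region or diabetes, so its exposure contrast may be biased and its predictions cannot vary by these factors

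*Combined protocol and SAP*

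**What the plan says.** All references are to the combined protocol and SAP.

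- **Statistical/analysis plan, ever versus never exposed.** The Cox model is "stratified by matched set to account for the matching". Absolute risk changes then come from "predictions from a Poisson model with the same covariates as our main Cox model, plus time since index date (time-updated").
- **Confounding subsection.** Two groups of variables are kept apart. The first is "Age, GP practice, diabetes status and calendar time are matching variables". The second is introduced by "Our models will also be adjusted for the following potential confounders evaluated at beginning of follow up" and consists of smoking, BMI, alcohol and index of multiple deprivation.
- **Study Population.** "Exposed patients will matched to up to four controls on age at first prescription (within 3 years in either direction), GP practice, diabetes status", with controls taking the index date of their exposed man.
- **Censoring.** Observation also ends at "prescription of a PDE5 inhibitor (for unexposed controls"), a rule that has no counterpart for exposed men.
- **Interaction subsection.** Age appears in a model only here, as possible "effect modification between exposure to a PDE5 inhibitor and age, smoking status and index of multiple deprivation score".
- **Limitations.** The analysis is complete-case.

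The plan does not say how the Poisson model handles the matching, or to which population its predictions refer. The section on changes from the protocol adds nothing on either point.

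**The concern.** A stratification factor has no coefficient and is not a covariate. The stratified Cox model controls age, practice, diabetes and calendar time because it compares men only within a matched set. Carrying the same covariates into an unstratified Poisson model carries over the four lifestyle and deprivation variables and leaves that control behind.

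Two things follow:

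1. The exposure contrast behind the absolute risk change depends on the matched groups staying balanced in person-time, which the design does not guarantee. It could then disagree with the Cox hazard ratio reported beside it.
2. The predicted baseline risk is the same for a younger and an older man, and for a man in the north and one in the south. Yet the Background section says rates are higher in the south and south west, and the Limitations section uses practice as a stand-in for sun exposure. An absolute change scales with baseline risk, so a single figure needs a stated population before it can be interpreted.

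**Working it through.** **Plan's own figure.** The plan gives no absolute-risk figure to reproduce. Its one design figure, a detectable effect of about 1.18, is not an input here.

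**Step 1: terms in each model, read literally.**

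| Factor | Cox model | Poisson model |
|---|---|---|
| Exposure | term | term |
| Smoking, BMI, alcohol, deprivation | terms | terms |
| Time since index | time scale (our reading) | term |
| Age, practice, diabetes, calendar time | matched-set strata | none stated |

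Time since index measures elapsed time. It does not carry age or calendar period at entry.

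**Step 2: when the omission does no harm.** With exactly four controls per exposed man and equal follow-up, both groups have the same age distribution of person-time. Under a true null, the Poisson rate ratio without age is then 1.00, whatever the age gradient.

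**Step 3: effect of a control shortage that depends on age.** All inputs are assumptions except the maximum of four controls:
- age at index in exposed men is normal, mean 58, SD 11;
- the melanoma rate is proportional to exp(b × age), with b = 0.03 or 0.05;
- the true rate ratio is 1 and follow-up is equal;
- men in one age range lose d = 1 or 2 of their four controls.

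Let P be the share of exposed men in the short range and Q the share of their expected events there. The rate ratio without age is then

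RR = (4 − dP) / (4 − dQ).

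*Shortage above 65.* P = 1 − Φ((65 − 58)/11) = 0.262. Q = 1 − Φ((65 − 58 − 121b)/11), which is 0.380 for b = 0.03 and 0.466 for b = 0.05.
- Three controls: 3.738/3.620 = 1.03 and 3.738/3.534 = 1.06.
- Two controls: 3.475/3.241 = 1.07 and 3.475/3.069 = 1.13.

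*Shortage below 50.* P = Φ((50 − 58)/11) = 0.234. Q = Φ((50 − 58 − 121b)/11), which is 0.145 and 0.101.
- Three controls: 3.766/3.855 = 0.98 and 3.766/3.899 = 0.97.
- Two controls: 3.533/3.710 = 0.95 and 3.533/3.798 = 0.93.

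The range is about 0.93 to 1.13, and the direction depends on which men are short of controls.

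**Step 4: wider assumptions.** With exposed age about N(59, 11) and rates rising 2-6% per year of age, omitting age gives:

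| Scenario | Rate ratio under a true null |
|---|---|
| Four controls; control follow-up 10-20% shorter at ages 50-69 | 0.985-1.000 |
| Controls falling from 4 to 3 with age | 1.01-1.03 |
| Falling from 4 to 2 | 1.03-1.08 |
| Falling from 4 to 1 | 1.05-1.16 |

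In a simulated matched cohort with controls falling from 4 to 2 and rates rising 2% or 4% per year, the ratio was 1.01-1.07 without age and 0.98-1.02 with age added (Monte Carlo standard error about 0.009).

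**Step 5: spread hidden by a prediction without age.** Between ages 40 and 75, a rise of 3-5% per year implies a rate difference of exp(35 × 0.03) = 2.9-fold to exp(35 × 0.05) = 5.8-fold. The model as written returns one rate for both.

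**The case against.** The strongest reply is that matching already does the work. Exposed and unexposed men are balanced at index on all four factors. Because a set shares its index date, the time-since-index term absorbs much of the drift in attained age and calendar time that shorter control follow-up would cause. This stands: control-only censoring moved the ratio by at most 1.5% in Step 4. The main route to bias is a number of controls that varies with a risk factor, and the documents do not show whether it does.

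The sizes rest on assumed gradients, ages and shortages, and even the sign is open. That also stands. For scale, 0.27% of 179,298 is about 484 exposed cases, if the stated prevalence is read as events. At 1:4 under the null, the standard error of the log rate ratio is √(1/484 + 1/1936) = 0.05. A loss of one control in four is therefore about one standard error or less; a loss of two can be more.

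The plan promises changes in absolute risk, not age-specific risks, and an average over a balanced cohort can be valid without an age term. This is fair, so the spread in Step 5 is lost detail and not bias in itself. The average still needs a named population.

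Finally, the word 'also' in the confounding subsection may mean that the matching variables were intended for every model. That is possible, but the sentence defining the Poisson model does not say so.

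**Conclusion.** The point holds as a weakness in the specification of a supporting output. As written, the Poisson model has no term for age, calendar period, region or diabetes. Its predictions cannot vary by these factors, and it names no reference population. These statements follow from the text alone.

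Bias in the exposure contrast is possible, not shown. It is nil with a constant ratio and similar follow-up. With rates rising 3-5% per year of age and a loss of one or two of four controls in one age range, it runs from about 0.93 to 1.13 under a true null; if controls fell from four to one with age, at 2-6% per year, it would reach 1.05-1.16. Only age was worked through in full here.

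A reader might infer that the absolute risks are confounded, or that the study's main result is compromised. The documents support neither. They give no data on imbalance, and the stratified Cox hazard ratio does not depend on the Poisson model.

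**What to change.** State that the Poisson model includes age (preferably current age, in time-updated bands or a spline), calendar period, diabetes and practice region, alongside the Cox covariates and time since index date. State also that predictions with and without exposure are averaged over the covariate distribution of the exposed men.

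An alternative is to apply the adjusted Cox hazard ratio to age-specific rates in the unexposed. This keeps the absolute and relative results consistent with each other.

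Reporting by age band is optional.

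The cost is a sentence or two in the plan and a few more model terms. Age, region and diabetes status are already in the descriptive analyses, and calendar period follows from the index date. No new data are needed.

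### Age is matched only to within 3 years and the set-stratified Cox models carry no age term; adding age at the index date would remove any remaining within-set imbalance at almost no cost (minor)

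*Combined protocol and SAP*

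**What the plan says.** Under Study Population, each exposed man is "matched to up to four controls" on "age at first prescription (within 3 years in either direction), GP practice, diabetes status", and controls take over the exposed man's index date. Timing is fixed by the sentence "All matching variables will be measured at the index date". Only age carries a tolerance.

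Under Statistical/analysis plan, observation time starts at the index date, so age is not the time scale. The Cox model is "stratified by matched set to account for the matching".

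The Confounding part classes age with the design variables and then turns to the covariates: "Age, GP practice, diabetes status and calendar time are matching variables. Our models will also be adjusted for the following potential confounders evaluated at beginning". The four items listed are smoking status, BMI, alcohol status and deprivation score. The cumulative-prescription models re-run the same analysis with a different exposure variable.

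Age appears in two other places. It is described by exposure group in the descriptive analyses, and it is one of three potential effect modifiers to be explored by interaction terms. The Limitations section does not discuss residual age differences. The closing section on changes from the protocol adds an exclusion of men without a consultation in the year before the index date, but reports no age term.

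**The concern.** Stratifying by matched set removes whatever is constant within a set. Practice, diabetes status and index date are constant; age is not. A control may differ from the exposed man by 3 years, and two controls in one set may differ from each other by 6. With no age covariate, nothing in the model accounts for that remainder.

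If the differences average out across sets, little follows. If exposed men are systematically older or younger than their controls, part of the age gradient in melanoma enters the primary hazard ratio and the cumulative-prescription hazard ratios.

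A symmetric caliper does not by itself guarantee a zero mean gap, because the gap depends on how eligible controls are spread inside the window. Two features of the design could tilt that spread. Controls must not yet have started the drug and are censored when they do. The added consultation exclusion also fell mainly on unexposed men.

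The exposure-by-age interaction is a related loose end. Smoking and deprivation score, the other two modifiers, are already in the covariate list as main effects. Age is not, and the plan does not say that it would be added.

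**Working it through.** **Figures in the plan.** The plan gives no figure for residual age imbalance, so there is none to reproduce on the point itself. Its only effect-size figure is the detectable ratio of about 1.18 under Sample size/power calculation (179,298 men per group, 0.27% with melanoma, 1:1, 80% power, 5%; two-sided assumed). With a pooled two-proportion test:

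- Proportions: 0.0027 and 0.0027 × 1.18 = 0.003186; difference 0.000486; mean 0.002943.
- Standard error: √(2 × 0.002943 × 0.997057 / 179,298) = 0.000181.
- z = 0.000486 / 0.000181 = 2.69; power = Φ(2.69 − 1.96) = 76.6%.
- The ratio giving 80% power is 1.188.

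This is slightly above a figure that the plan calls approximate, and it does not bear on the age question.

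**Inputs for the age question.**

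- From the documents: caliper ±3 years; up to four controls per exposed man; no age term.
- Assumed: melanoma rate rises 3-5% per year of age.
- Assumed: the density of eligible controls inside the window is either flat or thins with age at 4-10% per year.

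**Step 1, mean gap.** If control density is proportional to exp(−g·x) for x from −3 to +3 years, controls are younger on average by 3·coth(3g) − 1/g, which is close to 3g:

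- g = 0: 0 years
- g = 0.04: 0.12 years
- g = 0.10: 0.30 years

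**Step 2, shift in the hazard ratio.** To first order the factor is (1 + annual rise)^gap:

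| Mean gap (years) | 3% per year | 5% per year |
|---|---|---|
| 0 | 1.000 | 1.000 |
| 0.12 | 1.004 | 1.006 |
| 0.30 | 1.009 | 1.015 |
| 0.50 | 1.015 | 1.025 |

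The last row is a stress case. Under the thinning model it needs a pool falling about 17% per year of age, outside the assumed range.

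**Step 3, allowing for the spread of ages as well as the mean.** This uses log-hazards of 0.02-0.06 per year of age, a wider range than above:

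- Flat control density: factor 0.995-0.999.
- Density falling 5-10% per year of age: factor 1.002-1.013.
- Density rising 5% per year of age: factor 0.986-0.996.

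The sign depends on an input that the documents do not supply.

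**Step 4, comparison with sampling error.** Reading 0.27% of 179,298 as exposed events gives about 484. Four controls each at a similar rate give about 1,936 unexposed events. Then:

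- SE(log HR) ≈ √(1/484 + 1/1,936) = 0.051.
- Smallest non-zero shift: 0.12 × ln 1.03 = 0.0035, or 0.07 SE.
- Largest: 0.30 × ln 1.05 = 0.0146, or 0.29 SE.

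Fewer controls per set would raise the SE and lower these fractions.

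**Step 5, gap needed for age alone to produce 1.18.** ln 1.18 = 0.1655.

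- At 3% per year: 0.1655 / 0.0296 = 5.6 years.
- At 5% per year: 0.1655 / 0.0488 = 3.4 years.

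Both exceed the caliper.

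**The case against.** The best defence is that a symmetric 3-year caliper with set stratification already does nearly all the work. Every input that drives a non-zero shift is assumed. The consultation exclusion could narrow a gap as easily as widen one, since the section describing it says nothing about the excluded men's ages. All of this stands, and it is why the point is minor.

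It may also be said that the descriptive analyses would expose a material gap, and that fitting an age main effect beside an age interaction is ordinary practice. The first is partly right. However, a comparison of exposed and unexposed men overall is not the within-set difference, particularly when sets have between one and four controls. The second is reasonable, but the plan does not state it.

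Three stronger readings are tempting, and the documents support none of them:

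- **The hazard ratio is biased.** That needs a systematic within-set gap, which the documents do not show.
- **Age could rival the effect that the study is powered to find.** A set at the very edge of the window would have an age-related ratio of 1.03³ = 1.09 to 1.05³ = 1.16. Setting that beside 1.18 compares one extreme set with a study-wide average, and step 5 shows that the caliper rules out the equivalence at these gradients.
- **The plan regards age as completely dealt with by matching.** It only names age as a matching variable and leaves it off the covariate list.

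**Conclusion.** The observation holds as a minor point. The plan controls age to within 3 years and makes no provision for what remains inside a set.

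If the rate rises 3-5% per year of age and controls average 0-0.3 years younger, the hazard ratio moves by about 0-1.5%, at most about 0.3 of a standard error. If controls were older on average, the shift would go the other way. The age gradient and the gap are both assumptions, and the standard error rests on reading the plan's 0.27% as an event proportion.

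No conclusion of the study is put in doubt. The reason to act is that the adjustment costs almost nothing and settles a question that readers cannot settle from the planned output.

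**What to change.** 1. Keep the 3-year caliper.
2. Add continuous age at the index date, linear or as a spline, to the covariates of the set-stratified Cox models for ever-exposure and for cumulative prescriptions.
3. State that age at the index date is the main effect in the exposure-by-age interaction model.
4. Report the mean within-set age difference (exposed man minus the mean of his controls) after the consultation exclusion. If it is close to zero, the matter is closed.

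The cost is one covariate, or a few for a spline. Age at the index date is already held for every man because he was matched on it, so no patients are lost to missing data and the loss of precision is negligible.

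The absolute-risk Poisson model is defined by reference to the Cox covariates, so the added term would carry into it. How that model otherwise accounts for the matching is a separate question that the section leaves open.
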